### Surgical technique

All patients underwent RAE or MIE (McKeown procedure) with two-field lymphadenectomy by the same experienced surgeons who had entirely completed the learning curve in each center. A surgeon who accomplished 40 cases of RAE or MIE annually is determined to be sufficiently skilled for our study. RAE is completed using Da Vinci surgical system (Intuitive Surgical, Inc., Sunnyvale, CA, USA) and MIE is carried out with a thoracoscopic-laparoscopic system.

For RAE, the procedure in details has been described in our previous article [22]. For the thoracic phase, patients are placed in the left semi-prone position and trocars arrangement are presented in Fig. 2a. The mediastinal pleura above the arch of the azygos vein is divided firstly. Lymph nodes along the right-RLN and the superior esophagus are dissected en bloc. Then the dissection continued from the right main bronchus up to the plane between the esophagus and the trachea membrane. Lymphadenectomy is performed along the left-RLN from the thoracic outlet to the aortic-pulmonary window. The subcarinal lymph nodes will be dissected after this step, and the lower esophagus is dissected to the hiatus. For the abdominal phase, patients are placed in the reverse Trendelenburg position, and the robotic cart will be docked from the head side of the patient. Five ports are used in the abdominal stage, including one observation port, two robotic arm ports and two assistant ports (Fig. 2b). The greater curve is dissected firstly until the short gastric artery. The celiac area is dissected and the left gastric artery is cut off. Then the operation converts to the hepatogastric ligament, in which the right crus, left crus as well as fundus are dissected. A small incision is made at the sub-xiphoid and a narrow gastric tube (3–4 cm) will be made from the abdomen. Finally, the anastomosis is completed at the neck.

**Fig. 1 Fig1:**
[figure not shown]
Flow chart of the RAMIE trial

**Fig. 2 Fig2:**
[figure not shown]
Trocars arrangement during the process of RAE and MIE. **a** thoracic part of RAE. **b** abdominal part of RAE. **c** thoracic part of MIE. **d** abdominal part of MIE. The images depicted in Fig. 2 derive from our own source

For MIE, the procedure in details has also been published in previous article [23]. Trocars for the thoracic phase are placed as followed: the 7th intercostal of the right anterior axillary line is set as the observation port, the 3th intercostal is set as the primary operation port, the 6th intercostal of the right midaxillary line is set as the secondary operation port, and the 9th intercostal of the right midaxillary line is set as the operation port for the assistant surgeon (Fig. 2c). Trocars arrangement for the abdominal phase is shown in Fig. 2d. As in the RAE, the MIE procedure consists of thoracoscopic mobilization of the esophagus, which was followed by laparoscopy with creation of the gastric tube and cervical esophagogastric anastomosis.

### Study endpoints

#### Primary endpoint

The primary endpoint is the 5-year overall survival (OS) time. OS is defined as the time from the date of surgery to the day of death or to the last follow-up [24].

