## Methods

### Study design

This is a prospectively randomized controlled trial to assess the comparison between RAE and MIE in the treatment for patients with ESCC. According to previous studies, the long-term survival results of RAE seemed to be comparable but not inferior to the MIE or open esophagectomy [19, 20]. Therefore, the present study was designed as a non-inferiority trial, which was based on the hypothesis that the 5-year overall survival in the RAE is uncompromised with MIE. To achieve the primary goal, 360 patients with ESCC will be recruited from 4 high-volume centers (> 100 cases of combined approaches annually) in China. Based on the volume of esophagectomy in our center, 120 patients will be scheduled for this trial and approximately 5 patients will be enrolled for each group per month. For the other three centers, the estimated enrolled patients will be 2 for each group per month. The flow chart of this trial is presented in Fig. 1. The study has been approved by the ethics committees of participating institutions, as well as in accordance with the principles of the Declaration of Helsinki and Good Clinical Practice Guidelines. Written informed consent is obtained from each participant.

Neoadjuvant therapy will be used as a stratification factor in this study. After finishing preoperative treatment, patients will be restaged and confirmed to suitable for surgery by multidisciplinary team (MDT) of clinicians. When the tumor is considered as resectable, patients will undergo the randomized intervention - either RAE or MIE depending on randomization.

The study started on July 2017. Enrollment will take about 2 years and follow-up for will be 5 years. So the total duration of this study will lasts 7 years.

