### Randomization

Randomization will be performed via a computer-generated random numbers sequence and further stratified by whether the patient has undergone neoadjuvant treatment or not. Considering the unfeasibility in clinical practice, no blinding will be set for the patients and surgeons. Nevertheless, the independent study team is blinded to the allocation.

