#### Secondary endpoints

5-year disease-free survival (DFS) time: DFS is defined as the time from the date of surgery to the day of tumor recurrence, tumor progression or patients’ death assessed up to 5 years [24].3-year OS and DFS.Quality of life (QOL): QOL is assessed among patients by using the European Organization for Research and Treatment of Cancer Quality of Life Questionnaire C-30 (EORTC QLQ-C30) and EORTC QLQ-OES18 at randomization, and 3 month, 6 month, 9 month and yearly till 3 years after surgery respectively.Short-term outcomes: Short-term outcome refers to operation related index during the perioperative period, which includes operative time, total blood loss, R0 resection rate, total and positive numbers of dissected lymph nodes, 30- and 90-day postoperative mortality, length of hospital stay and ICU stay, postoperative recovery, and the incidence of treatment-related complications. True operation time is defined as time from incision until finally closure (minutes), and in which the time of docking and undocking robot was removed. We also assess the total operative time in which docking and undocking time was included. Postoperative recovery is defined as the days of chest tube and other surgical drainages removed, and the days until first ambulation and oral intake. First ambulation was defined as when the patient could continuously walk for at least 10 m, and first oral intake was when the patient could first eat gelatin or semi-solid food. The complications were diagnosed and defined according to the International Consensus of Esophagectomy Complications Consensus Group (ECCG) [25] (shown in Table 1).

**Table 1 Tab1:** Definitions of complications

Pulmonary	
Pneumonia: Radiographic confirmation with positive respiratory tract culture.	
Pleural effusion: Pleural effusion requiring additional drainage procedure.	
Pneumothorax: Radiographic confirmation requiring chest tube reinsertion.	
Respiratory failure: Reintubation or tracheostomy for weaning failure.	
Atelectasis: Atelectasis mucous plugging requiring bronchoscopy.	
Cardiovascular	
Cardiac arrest requiring CPR	
Atrial arrhythmia: Electrocardiographic (ECG) confirmation of atrial arrhythmia.	
Deep venous thrombosis: Ultrasound confirmation of deep venous thrombosis.	
Myocardial infarction: Confirmed by ECG changes, information with cardiac biomarkers and symptoms of ischaemia.	
Gastrointestinal	

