### Assessment and follow-up

Pre-treatment assessment is performed by routine examinations including a physical examination, standard laboratory tests, a CT scan of the thorax and abdomen (or PET/CT), upper gastrointestinal contrast, upper endoscopy with biopsies and endoscopic ultrasound. For patients who had received preoperative neoadjuvant treatment, they will be restaged and confirmed to suitable for surgery by clinicians.

After surgery, follow-ups will be performed one time per 3 months in the first two years and one time per 6 months from the third year until the end of follow-up. Examination will be focused on laboratory tests (blood routine, tumor biomarker), CT scan, ultrasound, and quality of life questionnaires. For all patients, follow-up is carried out until the end of the trial or death.

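### OS and DFS are timed from surgery rather than randomisation, so the primary non-inferiority comparison is in effect restricted to operated patients

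*Protocol article*

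**What the plan says.** Under Primary endpoint, the article states: "OS is defined as the time from the date of surgery to the day of death or to the last follow-up". Under Secondary endpoints it uses the same origin: "DFS is defined as the time from the date of surgery to the day of tumor recurrence".

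Randomisation is a separate and earlier event. Study design says: "When the tumor is considered as resectable, patients will undergo the randomized intervention - either RAE or MIE depending on randomization". Quality of life is collected "at randomization, and 3 month, 6 month, 9 month and yearly till 3 years after surgery respectively", which treats randomisation and surgery as two time points. The Randomization section says that "no blinding will be set for the patients and surgeons"; only an independent study team is blinded. It also says that allocation is "further stratified by whether the patient has undergone neoadjuvant treatment or not".

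Scheduled visits are tied to the operation: "After surgery, follow-ups will be performed one time per 3 months in the first two years". The Statistical analysis section names Kaplan-Meier and the log-rank test. Sample size considerations names a non-inferiority log-rank test with an upper bound of 1.33. The article gives no start date for a patient who is randomised but not operated on, no expected number of such patients, and no interval between randomisation and surgery.

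**The concern.** Randomisation makes the arms comparable on the day of allocation. Whatever happens between that day and the operation can depend on the arm, because patients and surgeons know the allocation. A patient who withdraws, progresses, deteriorates or dies in that interval has no time zero under the printed definition. These reasons are likely to be related to prognosis. Even among operated patients, unequal waits would start the two arms at different points.

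In a non-inferiority trial the risk has a clear shape. If poor-prognosis patients are lost mainly from RAE, the HR for RAE versus MIE is pulled downwards and non-inferiority becomes easier to claim. If they are lost mainly from MIE, the opposite happens. A larger sample cures neither.

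**Working it through.** **Step 1. The definition.** The origin is surgery. Allocation precedes surgery. No substitute origin is given. So a randomised, unoperated patient has no OS or DFS value, and a pre-operative death has no place in the Kaplan-Meier curve. This needs no arithmetic.

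**Step 2. The plan's own figure.** Inputs from Sample size considerations: margin 1.33, power 0.80, significance level 0.05 (sidedness not stated), hazard rate 0.60 (read as per year), 5% loss per year, 2 years of accrual plus 5 of follow-up. True HR is taken as 1.

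- Schoenfeld events, one-sided: 4(1.645 + 0.842)² / (ln 1.33)² = 304.1. Freedman events: (1.645 + 0.842)² × (2.33/0.33)² = 308.2.
- Probability of an observed death, with λ = 0.60 and δ = −ln 0.95 = 0.0513: λ/(λ+δ) × [1 − (e^(−5(λ+δ)) − e^(−7(λ+δ))) / (2(λ+δ))] = 0.901.
- N = 304.1/0.901 gives 338. N = 308.2/0.901 gives 342, and 342/0.95 gives 360.

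The stated 360 is thus recovered only as a one-sided 0.05 variant with a further 5% allowance. The point made here does not rest on that figure.

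**Step 3. Power.** Power = Φ(√events/2 × ln 1.33 − 1.645). With all 360 patients there are 324 events and power is 82.2%. With an assumed 2% lost it is 81.5%, with 5% lost 80.5%, and with 10% lost 78.6%. The power cost is small; bias is the issue.

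**Step 4. Bias, with assumed losses in RAE only.** Let a share q of RAE be unoperated with hazard λu and the rest have hazard λo, so S₁(t) = q·e^(−λu·t) + (1−q)·e^(−λo·t) with density f₁. The MIE arm has S₀ and f₀. The large-sample Cox HR e^β solves ∫[f₁(1−w) − f₀w]G dt = 0, with w = e^β S₁/(e^β S₁ + S₀). G is follow-up ending uniformly between 5 and 7 years with loss hazard 0.05. The interval from randomisation to surgery in operated patients is ignored.

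Assumptions:
- q is 4/180 (2.2%) or 9/180 (5%).
- The background is either 59% 5-year OS (the MIE figure cited in the Discussion; hazard −ln 0.59/5 = 0.106 per year) or the literal 0.60 per year.
- Unoperated patients either die early (hazard 3 per year, 1 − e^(−3) = 95% dead at one year) or have three times the operated hazard.

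In the table, "All HR" and "Op. HR" mean the HR in all randomised and in operated patients.

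| Background | Unoperated | Lost | All HR if Op. HR = 1 | Understated | Op. HR if All HR = 1.33 | Understated |
|---|---|---|---|---|---|---|
| 59% at 5 y | early deaths | 4 | 1.052 | 5.0% | 1.28 | 4.0% |
| 59% at 5 y | early deaths | 9 | 1.120 | 10.7% | 1.21 | 9.2% |
| 59% at 5 y | 3× hazard | 4 | 1.028 | 2.7% | 1.30 | 2.4% |
| 59% at 5 y | 3× hazard | 9 | 1.063 | 5.9% | 1.26 | 5.4% |
| 0.60/y | early deaths | 4 | 1.020 | 1.9% | 1.31 | 1.6% |
| 0.60/y | early deaths | 9 | 1.045 | 4.3% | 1.28 | 3.6% |
| 0.60/y | 3× hazard | 4 | 1.016 | 1.6% | 1.31 | 1.4% |
| 0.60/y | 3× hazard | 9 | 1.037 | 3.6% | 1.29 | 3.3% |

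**Step 5. Other patterns of loss.** With 5% lost in each arm and no true difference there is no bias. If the HR in all randomised patients is 1.33, the operated-only HR is 1.34-1.37, which is slightly against a non-inferiority claim. With 5% lost in MIE only and equal hazards in operated patients, the HR in all randomised patients is 0.89-0.96. The operated-only value of 1.00 is then unfavourable to RAE.

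**The case against.** The strongest reply is that the article never says that unoperated patients are excluded. An analysis set, or a substitute start date, could stand in the full protocol or analysis plan, and the Assessment and follow-up section has all patients followed to death or the end of the trial. That is fair as far as it goes: exclusion is a consequence of the definition, not a stated rule. But the article does not leave the origin open. It prints one that exists only for operated patients, and any all-randomised analysis would have to override it.

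Three stronger readings are tempting, and the document does not support them.

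- A reader might infer that RAE patients wait longer because of robot availability. The article mentions no such constraint and no waiting time. Refusal after open allocation could equally come from MIE patients who wanted the robot.
- A reader might infer that randomisation precedes neoadjuvant therapy, leaving a gap of months. Stratifying by treatment already undergone, and describing restaging and team confirmation before the randomised operation, most naturally place randomisation afterwards. The flow chart is not available here to confirm it.
- A reader might divide lost patients by expected deaths. With about 73 deaths per arm at 59% 5-year OS, 4/73 = 5% and 9/73 = 12%, which would turn an HR of 1.33 into 1.26 or 1.17. That treats the HR as a ratio of counts and every lost patient as a death. Step 4 gives 1.28 and 1.21 even when nearly all die early, and 1.26-1.31 otherwise.

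**Conclusion.** The point holds as a badly fixed definition of the primary endpoint and of DFS. Its direction and size cannot be settled from the document, because no no-surgery rate is given. With an assumed 2-5% loss in RAE only, understatement of the HR is roughly 1-6% under moderate assumptions. It reaches about 9-11% only if nearly all lost patients die early and 5-year OS is about 59%. With equal loss there is little bias, and with more loss in MIE it reverses. If randomisation follows restaging, as seems likely, the interval may be short and the effect towards the low end. That lowers the expected harm but does not repair the definition. The document does not support a claim that the trial is biased towards non-inferiority.

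**What to change.** Define OS and DFS from the date of randomisation, in all randomised patients analysed as allocated. Define the DFS event for patients who are never resected, since recurrence has no meaning for them. Keep time from surgery in operated patients as a sensitivity analysis. State that randomisation follows restaging and multidisciplinary confirmation of resectability, if that is the intended order.

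No extra patients are needed, since all 360 then count. The change is more than wording. It amends the primary endpoint definition in a trial that had recruited 210 patients by 1 December 2018 and was still recruiting. It should therefore be documented and made before the survival data are compared by arm. It also needs vital-status follow-up of the few unoperated patients, for whom the article schedules no visits because it times them from surgery.

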#### Secondary endpoints

5-year disease-free survival (DFS) time: DFS is defined as the time from the date of surgery to the day of tumor recurrence, tumor progression or patients’ death assessed up to 5 years [24].3-year OS and DFS.Quality of life (QOL): QOL is assessed among patients by using the European Organization for Research and Treatment of Cancer Quality of Life Questionnaire C-30 (EORTC QLQ-C30) and EORTC QLQ-OES18 at randomization, and 3 month, 6 month, 9 month and yearly till 3 years after surgery respectively.Short-term outcomes: Short-term outcome refers to operation related index during the perioperative period, which includes operative time, total blood loss, R0 resection rate, total and positive numbers of dissected lymph nodes, 30- and 90-day postoperative mortality, length of hospital stay and ICU stay, postoperative recovery, and the incidence of treatment-related complications. True operation time is defined as time from incision until finally closure (minutes), and in which the time of docking and undocking robot was removed. We also assess the total operative time in which docking and undocking time was included. Postoperative recovery is defined as the days of chest tube and other surgical drainages removed, and the days until first ambulation and oral intake. First ambulation was defined as when the patient could continuously walk for at least 10 m, and first oral intake was when the patient could first eat gelatin or semi-solid food. The complications were diagnosed and defined according to the International Consensus of Esophagectomy Complications Consensus Group (ECCG) [25] (shown in Table 1).

**Table 1 Tab1:** Definitions of complications

Pulmonary	
Pneumonia: Radiographic confirmation with positive respiratory tract culture.	
Pleural effusion: Pleural effusion requiring additional drainage procedure.	
Pneumothorax: Radiographic confirmation requiring chest tube reinsertion.	
Respiratory failure: Reintubation or tracheostomy for weaning failure.	
Atelectasis: Atelectasis mucous plugging requiring bronchoscopy.	
Cardiovascular	
Cardiac arrest requiring CPR	
Atrial arrhythmia: Electrocardiographic (ECG) confirmation of atrial arrhythmia.	
Deep venous thrombosis: Ultrasound confirmation of deep venous thrombosis.	
Myocardial infarction: Confirmed by ECG changes, information with cardiac biomarkers and symptoms of ischaemia.	
Gastrointestinal	
Anastomotic leak: Full thickness defect involving esophagus, anastomosis, staple line, or conduit. Detection of saliva, ingested material, gastric secretions, or bile in the drain or wound.	
Conduit necrosis: Identified endoscopically. Extensive conduit necrosis has to be treated by conduit resection with diversion.	
Diaphragmatic hernia: Radiography confirm the presence of abdominal organs in the thoracic cavity, with or without gastrointestinal symptoms.	
Vocal cord palsy: Any sign of voice changes or aspiration. Confirmation and assessment should be by direct examination, sometimes laryngoscopy is necessary. Severe injury requiring acute surgical intervention (due to aspiration or respiratory issues).	
Chyle leak: Chyle test is positive in the thoracic drainage. Treated with enteric dietary modifications, total parenteral nutrition, and nterventional or surgical therapy.	
Wound infection: Local findings of erythema, drainage, subcutaneous emphysema, or tenderness requiring wound opening or antibiotics.	
Delirium: Transient confusion confirmed by disturbances in consciousness, cognition, and perception.	

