**Discussion:**

This is the first prospectively randomized controlled trial designed to compare RAE with MIE as surgical treatment for resectable ESCC. According to our hypothesis, RAE will result in at least similar oncologic outcomes and long-term quality of life, but with a shorter operation time, lower percentage of perioperative complications, lower blood loss, and shorter hospital stay when compared with MIE. This study started in July 2017. Follow-up will terminate after 5 years from the time when the last patient was enrolled.

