The advantage of robotic system gives surgeons greater confidence of achieving a complete bilateral RLN lymph nodes dissection, but this may increase the incidence of postoperative RLN injury. Studies show the postoperative RLN injury rate range from 9.1 to 20.6% in RAE group as from 3.8 to 29.4% in MIE group, there is no significant difference between the two groups [19, 27, 28, 30]. The left RLN injury is more common than the right RLN. Notably, RLN injury can be caused by contusions, excessive stretching, and thermal damage occurring during manipulation. Chao et al. reported their method reducing the RLN injury by using the third robot arm (controlled by the operator) which allows achieving an excellent operating exposure through the application of stable and self-controllable tractions and countertractions on the esophagus and trachea [28].

Since robotic surgery has just begun to be accepted by thoracic surgeon, several groups show that the operation time of robot-assist esophagectomy is significantly higher than that of thoracoscopic esophagectomy, especially one-lung ventilation time [19, 30]. This has the potential to increase postoperative respiratory complications, but no significant increase in the risk of respiratory complications was identified in the RAE group. These studies also have found that no significant increase in the risk of anastomotic leakage, or other postoperative complication. For the reason that the surgeon can perform complex procedures sitting comfortably, they have not felt fatigued even if the prolong of operative time.

Although RAE is reported to improve the efficiency of lymph node dissection, it is unclear whether more extensive lymph node dissection could result in a significant survival advantage. Fewer studies were designed to focus on comparing long-term survival between RAE and MIE. Park et al. reported that the 5-year overall survivals were not different between the two groups (69% in RAE vs. 59% in MIE, *P* = 0.737). The 5-year freedom from locoregional recurrence was 88% in the RAE group and 74% in the MIE group, however the difference was not statistically significant (*P* = 0.100, 19]. The primary endpoint of our controlled trial is 5-year overall survival. According to our hypothesis, RAE will result in at least similar oncological outcomes and long-term quality of life compared with MIE.

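### The docking-free operation time favours RAE by exactly the docking time, and the article does not say whether it or total operative time bears on the expected shorter operation

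*Protocol article*

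**What the plan says.** Under Secondary endpoints, the short-term outcomes are introduced as a group "which includes operative time, total blood loss, R0 resection rate", among other items. Two time measures are then defined. The first, *true operation time*, runs in minutes from incision to closure, "in which the time of docking and undocking robot was removed". The second follows in the next sentence: "We also assess the total operative time in which docking and undocking time was included".

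Under Surgical technique, docking is described for RAE only ("the robotic cart will be docked from the head side of the patient"). MIE is done with thoracoscopic and laparoscopic equipment and has no robot to dock.

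The Discussion paragraph of the abstract says what the investigators expect of RAE beyond similar oncologic results and quality of life: "but with a shorter operation time, lower percentage of perioperative complications, lower blood loss, and shorter hospital stay when compared with MIE". It does not say which time measure is meant. The main Discussion reports that, in several earlier series, "the operation time of robot-assist esophagectomy is significantly higher than that of thoracoscopic esophagectomy".

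Under Statistical analysis, continuous variables are compared by t test or ANOVA at a 0.05 significance level.

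**The concern.** Docking and undocking are part of carrying out a robotic operation. Taking those minutes out of the RAE time, while MIE is counted in full from incision to closure, means the two arms are not measured on the same footing. If the two operations take equally long in total, the docking-free measure will still show RAE as quicker.

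Three features of the text make this more than a matter of taste. The one-sided measure is defined first and is the one labelled *true*. A shorter operation is the first of four short-term advantages named in the abstract. And the earlier evidence quoted in the Discussion points the other way, so the choice of measure could decide the direction of the reported result. With two measures and no stated priority between them, a report of a shorter robotic operation could rest on the definition and not on the surgery.

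**Working it through.** The article gives no figure on this point, so there is nothing to reproduce. The size of the effect can only be illustrated.

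**Step 1: direction and amount of the shift.** Let T be the mean total operative time in each arm and d the mean docking plus undocking time in RAE.

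- Difference on total time, MIE minus RAE: T(MIE) − T(RAE).
- Difference on docking-free time: T(MIE) − [T(RAE) − d] = T(MIE) − T(RAE) + d.

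The docking-free comparison is therefore shifted towards RAE by exactly d. On total time the shift is zero. This step needs no assumption beyond the definitions.

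**Step 2: chance of a significant result from the definition alone.** Inputs:

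- 180 patients per arm (Sample size considerations).
- Significance level 0.05 (Statistical analysis). Whether it is one- or two-sided is not stated; two-sided is assumed.
- Equal mean total times in the two arms: assumed.
- d of 10, 20 or 30 minutes, and a common SD of 40, 60 or 80 minutes: assumed ranges, as neither quantity is in the article.

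Formulas: SE = SD × √(2/180), and chance of a significant result favouring RAE ≈ Φ(d/SE − 1.96).

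Worked case, SD 60: SE = 60 × √(2/180) = 6.32 minutes.

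- d = 10: 10/6.32 = 1.58, and Φ(1.58 − 1.96) = 0.35.
- d = 20: 20/6.32 = 3.16, and Φ(3.16 − 1.96) = 0.88.

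Full range:

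| SD (min) | SE (min) | d = 10 | d = 20 | d = 30 |
|---|---|---|---|---|
| 40 | 4.22 | 66% | 99.7% | about 100% |
| 60 | 6.32 | 35% | 88.5% | 99.7% |
| 80 | 8.43 | 22% | 66% | 94.5% |

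With no shift, the chance of a significant result in that direction is 2.5%.

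**Step 3: if RAE really takes longer.** If total RAE time is longer by L minutes, the docking-free difference is d − L and the chance falls accordingly. For example, with SD 60, d = 20 and L = 10, the net shift is 10 minutes and the chance is 35% instead of 88.5%. If L equals d, the docking-free measure shows no difference on average, although the RAE operation is longer by L.

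**The case against.** The strongest reply is that the article is open about both measures. The sentence after the docking-free definition adds total operative time, on which the docking shift is zero, so any reader can see what docking contributes. The endpoint list speaks only of operative time, and nothing ties the abstract's expectation to the docking-free version. Being defined first does not make a measure the principal one. Which version of a secondary outcome carries the test is often settled in a full protocol or analysis plan, and neither is shown. Docking-free time is also a legitimate quantity in its own right.

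Much of this stands. A reader might infer that the expected shorter operation is biased in favour of RAE by construction. The documents do not support that, because it would require the expectation to be tested on the docking-free measure, and no section says so. The illustration also rests on assumed values and on equal total times, whereas the Discussion cites earlier findings of longer RAE times.

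What does not fall away is the definition itself. This is not detail left out for brevity: the article writes down a measure that can shorten one arm only, puts it first, calls it *true*, and leaves both measures available for a stated expectation that one of them favours by design.

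**Conclusion.** The point holds in a limited form. A between-arm comparison of docking-free time is shifted towards RAE by the mean docking plus undocking time; that follows from the definition. The expectation of a shorter operation is exposed to this shift because no measure is assigned to it, but it is not biased as written.

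The exposure could be material. Under the assumptions listed, a spurious significant advantage goes from the nominal 2.5% to 22–66% for 10 minutes removed and 66–99.7% for 20 minutes. These figures would be lower if RAE truly takes longer, and they should be read as a range and not as an estimate for this trial.

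The consequence is confined to one item among the secondary short-term outcomes. The primary endpoint, overall survival, and the sample size are untouched.

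**What to change.** State that total operative time, from incision to closure with docking and undocking included, is the measure for the between-arm comparison and for the expectation of a shorter operation. Report docking-free time as a supplementary descriptive measure, preferably under a neutral label such as *operation time excluding docking*.

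The cost is a change of wording. Both times are already planned, so no new data are needed and no sample-size work follows. The assignment should be made before operative times are compared between the arms.
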